#### Sample Size

We estimate that the study has 80% power to detect differences in the primary outcome measure described earlier between the 2 treatment arms with a Cohen *d* effect size of at least 0.5, given the prespecified sample size of 100 and at least 3 repeated outcome measures. We selected a planned sample size of 100 to balance pragmatics and novel treatment intervention, while ensuring a large enough sample size to detect clinically meaningful differences.

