#### Study Procedures

All patient participants downloaded the Bark app and went through the process of connecting their social media and electronic communication platforms to the app. To promote trust and participation in the study, we allowed patients to decide which platforms to connect to the Bark app. While patients retained final control of the decision, we explained to them that their most frequently used apps would provide the most relevant information. Patients were randomized within strata formed by treating clinicians in a 1:1 ratio with blocks of size 2 to either the dashboard intervention or TAU. The purpose of stratified randomization in blocks was to promote balance in the number of patient participants in the 2 treatment arms seen by each clinician, thereby reducing the impact of differences between treating clinicians on comparisons of patient outcomes between the 2 arms. For patients in the intervention arm, the electronic dashboard was delivered to the treating clinician before scheduled clinical visits. The clinician and patient collaboratively decided when and how to use the dashboard in the session during each clinical encounter. For patients in the TAU arm, the clinician did not receive a clinical dashboard for review. After the initial visit to download the Bark app, there were no more study-specific research visits. To be pragmatic and stay as close to the real-world setting as possible, patients continued to be seen by their clinician as clinically indicated. The first regularly scheduled clinic visit with their clinician after the patient consented and downloaded the Bark app was considered the study’s baseline visit. Patients were then followed through their clinical care for up to 6 months, and all study measures were completed during their regularly scheduled clinic visits.

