#### Statistical Analysis

The primary outcome of the trial is the difference in depressive symptoms measured by the PHQ-9 total score over the course of follow-up between the dashboard intervention and TAU arms. Secondary outcomes include differences in anxiety symptoms measured by the GAD-7 total score and in the more distal outcome of functioning, as measured by the SF-36 MHC. Because the PHQ-9 and GAD-7 were collected at each clinic visit and the SF-36 MHC at baseline and end of the study, there are repeated measures over time for each scale within individual patients. We plan to use random effects linear regression models to test for differences in scores on these measures between the 2 treatment arms. We will include fixed effects terms for the treatment arm as well as for time. Furthermore, we will consider including fixed effects terms for potential confounders, such as demographics (eg, age, sex, and race), and clinical factors, such as primary diagnosis and the number of clinic visits as an indicator of clinical severity. We will also include random effects for individuals to account for the correlation in outcome measures within repeated measures of the same individual as well as for clinicians, if indicated, to account for the potential clustering effects of treatment within clinicians. The primary statistical test of interest will focus on the fixed effects term for treatment, which will provide an estimate of the mean differences in the outcome measures between the 2 treatment arms, controlling for time. We will consider different functional forms of the time covariate and use the one that provides the best fit to the data on changes in score over time. Given that patients will be enrolled in the study regardless of their current mental health status and scores on these outcome measures, we consider the model in which we control for time to be the most appropriate test of differences between the treatment arms. However, we may consider examining interactions between treatment and time to see whether changes in the scores over time differ between the 2 treatment arms. We will use the conventional threshold of *P*<.05 to declare differences statistically significant.

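### The 80% power claim fits a test on post-baseline PHQ-9 scores; if baseline PHQ-9 is one of the repeated outcomes, as the primary model naturally reads, power at the three-measure minimum is about 43% to 62%

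*Protocol article*

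**What the plan says.** The Sample Size section of the protocol article states: "We estimate that the study has 80% power to detect differences in the primary outcome measure" for a Cohen d "effect size of at least 0.5", "given the prespecified sample size of 100 and at least 3 repeated outcome measures". It does not say whether baseline counts among the three.

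The Statistical Analysis section plans a random effects linear model with fixed effects for arm and time and a random effect for patient. It then says: "The primary statistical test of interest will focus on the fixed effects term for treatment". A treatment-by-time interaction is optional. The candidate adjustment terms are demographics, primary diagnosis and number of visits; the baseline score is not among them.

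Four other statements bear on whether baseline PHQ-9 is an outcome:

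- Study Procedures defines baseline as the first regular clinic visit after consent and app download, and says that "patients continued to be seen by their clinician as clinically indicated".
- Table 1 ticks PHQ-9 only under the every-visit column; Patient Measures confirms that it is taken at baseline and at each later visit.
- Statistical Analysis counts the baseline SF-36 MHC as one of that scale's repeated measures, and the same model serves all three scales.
- Data Management says that patients complete the PHQ-9 before each visit.

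**The concern.** A treatment main effect without an interaction is one arm difference averaged over every outcome row in the model. If the pre-intervention score is one of those rows, its expected arm difference under randomization is zero, and it pulls the average towards zero. The power statement gives no sign of allowing for this.

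Two things are at stake. A real benefit could be missed by a test weaker than the one for which power was claimed. And a null result would be set against a stated 80% power for d = 0.5 that the test may not have had.

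**Working it through.** **Inputs from the protocol article.** 100 patients, allocated 1:1, so 50 per arm; d = 0.5; at least 3 repeated measures; threshold 0.05.

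**Assumptions.** Two-sided test; equal correlation r between any two scores of a patient (r is not given, so a range is shown); equal variance at each visit; a constant arm difference of 0.5 SD at every post-baseline visit and zero at baseline. Power is from the noncentral t distribution.

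**Step 1. The plan's own figure.** One measure per patient gives 69.7% power. The standardized difference needed for 80% with 50 per arm is 0.566. The mean of k scores has variance factor (1 + (k − 1)r)/k. With three post-baseline scores, 80% therefore requires

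(1 + 2r)/3 ≤ (0.5/0.566)² = 0.781, so r ≤ 0.67.

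The normal approximation gives a limit of 0.69. At r = 0.5, 0.6 and 0.7 power is 86%, 82% and 79%. The stated 80% is therefore reproducible for a test on three post-baseline scores with no loss. With 80 patients (an assumed 20% loss) the same three values become 77%, 73% and 70%.

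**Step 2. Baseline as one of the outcomes.** With m post-baseline visits plus baseline, the expected main effect is 0.5 × m/(m + 1) and the variance factor is (1 + m·r)/(m + 1).

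At the three-measure minimum, m = 2: effect = 0.5 × 2/3 = 0.333; variance factor = (1 + 2r)/3. At r = 0.5 the factor is 0.667, the standardized effect is 0.333/√0.667 = 0.408, and power is 52%.

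| Outcome rows | r = 0.3 | r = 0.5 | r = 0.7 | r = 0.8 |
|---|---|---|---|---|
| Baseline + 2 visits | 62% | 52% | 45% | 43% |
| Baseline + 3 visits | 77% | 65% | 56% | 52% |
| Baseline + 8 visits | 95% | 84% | 73% | 68% |

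With baseline plus two visits, 80% is reached only if r is about 0.02 or less. A mixed-model simulation of 300 runs per setting agreed: 54% and 46% for baseline plus two visits at r = 0.5 and 0.7, against 87% and 80% for three post-baseline scores.

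**Step 3. Baseline as a covariate.** Adjusting the mean of m post-baseline scores for baseline gives variance factor (1 + (m − 1)r)/m − r², and the effect stays at 0.5. For m = 2 and r = 0.3 the factor is 0.65 − 0.09 = 0.56.

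| Baseline covariate + 2 follow-up scores | r = 0.3 | r = 0.5 | r = 0.6 | r = 0.7 |
|---|---|---|---|---|
| 100 patients | 91% | 94% | 96% | 98% |
| 80 patients | 84% | 88% | 91% | 96% |

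These are the same three scores per patient as in the first row of the Step 2 table. Only their role in the model differs.

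**The case against.** The strongest reply is that the stated figure is not an arithmetic error: the usual repeated-measures formula returns 80% at a correlation near 0.7, and more at any lower value. That stands. A reader might infer that the 80% is simply wrong, or that it needs unusually favourable conditions. The article supports neither reading, because it gives no correlation and 0.67 is not an extreme limit.

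Nor does the article say outright that baseline PHQ-9 enters as an outcome. It defines the primary outcome as a difference over the course of follow-up and names baseline explicitly as a repeated measure only for the SF-36 MHC. Exclusion of the baseline PHQ-9 is therefore possible. What tells against it is that baseline is itself a regular clinic visit, that PHQ-9 is described as collected at each visit, that one model serves all scales, and that no baseline covariate is listed.

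Third, the claim is for "at least 3 repeated outcome measures", and many patients in ongoing psychotherapy may have more. This also stands: power near a coin toss belongs to the minimum, not to the trial as a whole. It does not remove the gap, since baseline plus three visits still falls short of 80% at every correlation in the table.

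Fourth, d = 0.5 might be meant as the difference in the tested term itself, already averaged over baseline. The dilution would then be built in, but with three measures the post-baseline difference would have to be 0.5 × 3/2 = 0.75 SD, which the section does not say.

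Finally, omitting the correlation and a loss allowance from a condensed article is no fault, and none is alleged here. Clinician clustering adds nothing to the concern either: "Patients were randomized within strata formed by treating clinicians in a 1:1 ratio with blocks of size 2", so a clinician intercept largely cancels from the arm contrast.

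**Conclusion.** The concern holds conditionally. The 80% is right for three post-baseline scores, no loss and a correlation up to about 0.67 (0.69 by the normal approximation). If baseline PHQ-9 is among the outcomes, which is the natural but not the only reading of Statistical Analysis, and if d = 0.5 is the post-baseline difference, power at the three-measure minimum is about 43% to 62% for correlations of 0.8 to 0.3. It rises with more visits but passes 80% only with many visits or a low correlation.

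The result rests on equal correlation between scores and a constant effect after baseline. The correlations and the 20% loss are assumed values, not figures from the article. The defect is a mismatch between the power statement and the role the model gives to baseline.

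**What to change.** In Statistical Analysis, state that post-baseline PHQ-9 scores are the outcomes and that baseline PHQ-9 is a covariate, keeping the treatment main effect as the primary test. The Sample Size claim of 80% for d = 0.5 is then safe with as few as two follow-up scores per patient, even with 80 evaluable patients, for correlations of 0.3 and above. GAD-7 and SF-36 MHC can be handled in the same way.

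If the main-effect model with baseline among the outcomes is kept, restate the power in Sample Size for that test, giving the assumed correlation and the number of visits.

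The cost is a sentence or two. The baseline scores are already scheduled for collection and no further patients are needed. Because the article reports data collection as complete, the choice should be recorded before the arms are compared; if that comparison has already been made, the results paper should say when the choice was made.

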### Ethical Considerations

The study protocol was approved by the Johns Hopkins University School of Medicine Institutional Review Board (#00184638). We obtained informed consent from both patients and clinicians who participated in the study, ensuring voluntary participation and understanding of objectives, procedures, and potential risks of the study. We obtained assent from patients who were aged <18 years and consent from their guardians. All personal data collected were anonymized and stored in encrypted electronic databases, accessible only to the research team members. To compensate participants for their time and effort, patients received US $100 at randomization and another US $100 at the completion of the study. Participants who shared iOS text data were compensated US $50 because of the extra work required from the participants to share these data. Therapists received US $100 for enrolling 5 patients, US $200 for enrolling 10 patients, and US $250 for enrolling ≥15 patients.

## Results

The study was initiated in April 2019, but progress was delayed due to the onset of the COVID-19 pandemic. Data collection has been completed, and the study results will be reported in a separate manuscript. The study is registered on ClinicalTrials.gov (NCT03925038).

## Discussion

### Challenges

#### Overview

The goals of this study were to create an electronic communication dashboard and evaluate its use in routine mental health treatment for patients aged ≥12 years with mood or anxiety disorders. The integration of a dashboard to monitor social media use in routine mental health care is novel and promising. With the explosion in the use of electronic communications, it is increasingly relevant to consider social media activity in the therapy setting to aid in treatment planning. However, there are important challenges that merit consideration in deciding how to best achieve this and testing whether doing so is acceptable and effective. In this study, we report the decisions we made to address these challenges in designing and testing such an intervention. The challenges generally fall into 3 categories: technological, ethical, and pragmatic.

#### Technical Challenges

The most immediate questions to tackle are technological, including how to monitor social media and electronic communications and how to extract and present the information from these data for routine use in clinical care. Regarding the first question, we decided to collaborate with a private start-up company and use the Bark app as a tool for monitoring patients’ digital social activity. Our patients typically use several social media and electronic communications platforms, and we wanted to simultaneously track as many as possible to obtain a more comprehensive picture of their digital social activity. The Bark app offers the best out-of-the-box solution that meets our needs for monitoring the widest array of platforms and working with both the iOS and Android operating systems, which are widely used by our patients. However, there are challenges in working with Bark. The app was not designed for our use case; therefore, we worked with the company to make certain modifications, to make it suitable for our purposes. To give an illustrative example, we had to shut down all alerts from the app, especially ones that promoted the product, because we did not want to be seen as endorsing it commercially. In addition, there are unavoidable challenges to making connections with the different social media and electronic communication platforms through the Bark app that are beyond its control. The iOS and Android operating systems each present their own challenges to work with, but Apple devices, in general, have stricter controls in place. Bark has implemented certain workarounds to these controls, such as for capturing SMS text messages; however, these solutions can add extra burden to patients in using the app, and it is important to learn whether this impacted their willingness to engage with the intervention. Moreover, different social media and electronic communications platforms are constantly evolving their rules and application programming interfaces for third-party access to their data, which could potentially disrupt the connections made by our patients through the Bark app. We will learn what impact, if any, this had on fidelity to the intervention throughout the course of the study. Finally, our incentives are not always aligned when working with Bark. They are a commercial enterprise and understandably motivated to focus on developing a product that will appeal to their target customers, which are parents. By contrast, we wanted to use a tool that can be seamlessly integrated into clinical care and would appeal to both our patients and their clinicians. There is clearly some but not complete overlap in our interests, and it is an open question whether working with the Bark app is sustainable beyond the life of this study.

Regarding a solution to digest and present information about the patient’s digital social activity, we decided to develop a custom electronic dashboard. Bark has developed its own algorithms to analyze social media activity data and present alerts of concerning behavior to parents. However, we chose not to use Bark’s alerts because their algorithms are proprietary, and we could not clinically validate them. As there were no other options that met our needs at the time, we decided to develop our own approach. As part of future work, we will conduct a qualitative assessment to gather stakeholder feedback on the dashboard, which can inform the next generation of development.

#### Ethical Challenges

The next set of challenges to consider are ethical challenges. A major concern is how to ethically manage personal information often exchanged on social media and other electronic communication platforms. This concern is especially heightened because we were dealing with patients as young as 12 years, and we were processing potentially sensitive information about their mental health through a third-party commercial app. We worked closely with our technology team to develop several solutions to securely gather and store data in a way that protected the privacy and confidentiality of our patients. However, these solutions raised competing concerns about how to manage scenarios where collected data might contain information that a patient was at risk of harming themselves or others. In weighing the competing concerns about privacy against responding to actionable findings revealed by the collected data, we decided to err on the side of privacy. We sought to inform patients when they joined the study that the information gathered through the Bark app was not monitored in real time and would be reviewed when they met with their clinicians. The clinicians were able to directly address any concerns about the risk of harm to the patient or others that emerged from reviewing their digital social activity during clinical sessions.

Furthermore, there was concern that social media and electronic communications may reveal information about third parties who did not consent to be in the study, such as friends, families, or acquaintances. To address this concern, we used automated procedures to anonymize the content by replacing identified names with fictitious substitutes. While no procedures for scrubbing identifiers in text are 100% effective, this step helps to minimize the chances of inadvertently revealing third-party identities. Consistent with this thinking, we also opted not to analyze data from videos or pictures. The videos and pictures are likely a rich source of information about a patient’s mental health status; however, we decided to forgo such information again in favor of caution in protecting the patient’s privacy.

#### Pragmatic Challenges

The final set of challenges to consider are pragmatic challenges. It is one thing to implement procedures that ensure the intervention is ethically sound, but it is another thing to ensure patients and providers are comfortable using those procedures. We anticipate that trust is an important factor in the adoption and success of the intervention. To respect the patient’s choice and promote trust, we chose to let participants select which social media and electronic communications platforms they connected to the Bark app. We recognize that some patients may have decided not to connect to certain platforms they regularly use because they were uncomfortable sharing their activity on these platforms, and, as a result, we may have missed important information that is highly relevant to their mental health. However, we reasoned the potential risk was worth the benefit of giving patients control over participation in the study and building trust with the intervention. We sought to explain to the patients during the log-in process the value of sharing their commonly used platforms to encourage more complete engagement. Similar reasoning motivated our decision to mask any specific content (ie, SMS text messaging) that was extracted from the social media and electronic communication platforms and displayed on the dashboard. Moreover, we wanted to give patients a measure of control over how the intervention was used and allow them to decide when clinicians could review the content. Finally, we decided to let the clinicians and patients decide collaboratively whether and when to use the dashboard during the clinical encounter. We trained the clinicians on how to interpret and use the information on the dashboard, but we let them make the decisions with their patients on how it was used in actual care. We understand that this may result in variability across clinicians on how the intervention was used, but we opted to be pragmatic and give the clinicians and patients control over the use of the intervention to foster greater buy-in.

### Limitations

In addition to the challenges detailed earlier, there are several limitations to the study that will be important to consider when interpreting the findings that come from it. First, the dashboard we developed and tested is a first-generation product, which may have important limitations in functionality. For example, it is unable to distinguish sarcasm or specific kinds of speech, such as slang, that may be important to correctly interpret social interactions. In addition, it does not include nontext forms of communication, including images or emojis, which can be rich sources of information. It is possible that the functional limitations may negatively impact the efficacy of the intervention. It will be important in future work to continue improving the dashboard to address these functional limitations and achieve the full potential of its clinical utility. Second, there is potential for selection bias in the study participants and their sharing of social media and electronic communication data. Moreover, for those who agreed to participate, their use of social media may have been influenced if they knew it was being regularly monitored. These considerations may skew the findings and limit their generalizability. Information gathered during the conduct of the study from those who do and do not agree to participate may help inform the extent to which these biases influence the results.

